#### Primary outcome

The Functional Ambulation Category (FAC) is the primary endpoint for determining the existence of independent walking through a concise level assessment. Primary endpoints are evaluated once in the baseline (pre-treatment), 4 weeks after the baseline (post-treatment), and 4 weeks after the last treatment (follow-up), a total of three assessments (Table 1). FAC is a variable that was evaluated by dividing by 1 to 6 depending on the degree of need for assistance when walking, and FAC accounts for more than 55% as a result of the validity evaluation of the research paper on the rehabilitation robot in the 2017 Cochrane review. FAC level ranges from level 1 in “Nonfunctional” to level 6 in “Independent Level and Non-Level Surfaces.”

**Table 1 Tab1:** Content of outcome measurement

Treatment number							
Outcome measure	Pre	1w	2w	3w	4w	Post	F/U
Primary outcome							
FAC	X					X	X
Secondary outcomes							
RMI	X					X	X
Walking velocity	X					X	X
Waking capacity	X					X	X
MI	X					X	X
Berg Balance Scale	X					X	X
MBI	X					X	X
Step counting	X					X	X
Borg scale	X					X	X
Swing time asymmetry	X					X	X
Step length asymmetry	X					X	X
Propulsion asymmetry	X					X	X

*Pre* pre-treatment, *1w* five times per week for the first week, *2w* five times per week for the 2nd week, *3w* five times per week for the 3rd week, *4w* five times per week for the 4th week, *Post* post-treatment, *F*/*U* follow-up, *FAC* Functional Ambulation Category, *RMI* Rivermead Mobility Index, *MI* Motricity Index, *MBI* Korean version of the Modified Barthel Index

#### Secondary outcomes

Secondary endpoints are Rivermead Mobility Index (RMI), 10-m walk test (walking velocity), 6-min walk test (walking capacity), Motricity Index (MI), Berg Balance Scale, the Korean version of the Modified Barthel Index (K-MBI), step counting, Borg scale, swing time asymmetry, step length asymmetry, and propulsion asymmetry. These evaluations are conducted once on the baseline (pre-treatment), 4 weeks after the baseline (post-treatment), and 4 weeks after the last treatment (follow-up), a total of three assessments (Table 1).

The second endpoints have a total of 11 assessments. First, RMI evaluates motor skills, consisting of 15 questions step by step, depending on the level of bed rotation to running. A total of 15 questions are scored 1 point if yes or 0 if no, and the total sum of the questions is used as a result of the evaluation. Second, walking velocity is a 10-m walk test that measures the speed during 10-m walking, and the unit is meter per second (m/s). Similarly, the third walking capacity is a 6-min walk test that measures the distance that can walk for 6 min, and the unit is meter (m). The fourth MI is an item to be evaluated in a 1 to 99 point system by measuring the lower leg force level from the ankle to the knee. These assessment items consist of three questions, each with a score of 0/9/14/19/25/33 and the total sum of the scores as a result of the evaluation. The fifth Berg Balance Scale is an item that evaluates balance ability by 0 to 56 points. There are 14 questions in total, and each question is scored from 0 to 4 points and the total sum of the scores is used as the result of the evaluation. The sixth K-MBI evaluates the independence of daily activities from 0 to 100 points. This assessment item consisted of 10 questions and, similarly, the total sum of the scores is used as a result of the evaluation. The seventh step counting measures the total number of steps performed by the patient during the specified walk-through time using the same mechanical counter by the three institutes. The measured number of steps is then used as a result of the assessment. The definition of a walk is the number of times a foot touches the ground again. The eighth Borg scale uses Borg’s rating of perceived exertion. Perceived exertion is defined as how much effort it takes to move or exercise. This item evaluates the cognitive level of the subjective effort intensity of the participants in the exercise from 0 (no breathlessness at all) point to 10 (maximal) points. Lastly, the three evaluation items are measured by motion analysis devices. There are swing time asymmetry analyzing gait phase, step length asymmetry analyzing gait phase, and propulsion evaluation item analyzing propulsion.

In addition, 4 weeks after baseline (post-treatment), patients in the experimental and control groups are questioned on the usability assessment of the electromechanical-assisted gait training. Also, the therapist who gave the treatment is questioned. The goal of this assessment is to verify and supplement the assessment items by verifying the usability level of various types of walk-through electromechanical-assisted gait trainers and verifying the reliability and validity of the usability assessment.

Finally, during the follow-up evaluation, the patients receive a follow-up assessment questionnaire to determine if the patients are treated for a period of 4 weeks of follow-up observation.

### Motion analysis devices

In the evaluation of research, there are two types of motion analysis devices to be used.

HumanTrack (Rbiotech, 1806A_DA004_H1FS), a gait analysis system, is a machine capable of performing walking analysis only at a distance of 5–7 m without space restriction, and even a seriously ill patient using an assist instrument can be measured.

Freemed (Rbiotech, 1807A_MX20321) is a foot pressure measurement system that allows patients and ordinary people to evaluate static and dynamic foot pressure, walking, and balancing abilities. In the static inspection, load ratios in the medical/lateral and anterior/posterior directions can be analyzed by the distribution of the pressure in the sole, and in the dynamic foot low-pressure inspection, not only temporo-spatial parameters such as the ratio of the foot angle standing device (instance phase) and the swing phase, but also walking pressure, average visibility, and walking force are provided.

### Safety assessment

The physical content of the clinical alteration is reported by the auditors, practitioners, and patients at each visit. All indication, data of onset, and period are recorded.

### Sample size

The primary endpoint is the FAC difference before and after training. Data were available on this parameter from a previous trial (Hiroko Watanabe et al. 2014). Hiroko Watanabe et al. show a study on the improvement of stroke walking ability using the hybrid assisted limb (HAL), a representative device of the walking rehabilitation robot. According to the reference, the mean change in existing medical devices was 0.54 and 1 in the test group and HAL group. The newly developed medical device for use in this study was expected to produce about 25% better results in performance than in the HAL group, assuming a variation of 1.25. Therefore, it was assumed that the difference between the variation in the FAC of the test medical device and the comparator device was 0.71 and that the standard deviation was conservatively approached to assume the largest value of 1.4. Two-sided tests were used for sample size estimation. The number of participants per group to achieve overall power of 80% under the significant level of 0.05 is 65. To allow for a possible 10% dropout rate, 144 people were registered per group with 72 people.

### Statistical analysis

Categorical variables such as gender, joint problem disorder, the cause of the disability, and paralysis side in demographic and clinical characteristic information will be presented as *n* (%). The pre-homogeneity will be analyzed by the chi-squared test or Fisher’s exact test. Continuous variables such as age, height, weight, the possibility of expression of intention, and the lower limb spasticity MAS score will be expressed as mean ± standard error (SE) and range. The pre-homogeneity will be analyzed using Student’s *t*-test or Wilcoxon’s rank sum test depending on whether the normality assumption is satisfied.

For all continuous variables of primary and secondary outcomes, the post-treatment measurement results will present the technological statistics, the observed number of patients, mean, SE, and range and compare the differences between groups using Student’s *t*-test or Wilcoxon rank sum test depending on the satisfaction of the normality assumption. The comparison analysis of differences before and after treatment in the group will be conducted using either the paired *t*-test or Wilcoxon’s signed tank test depending on the satisfaction of the normality assumption. In analyzing continuous variables, analysis of covariance (ANCOVA) will be performed after setting the variables as covariates when there are variables that seem to require control in the pre-homogeneity results for demographic and clinical characteristics.

Additional details regarding subgroup and adjusted analyses and definition of analysis populations are available in the clinicaltrials.gov (KCT0003411) in the study summary.

All data will be analyzed using SAS version 9.4 or later. All statistical tests will be two-sided, and the level of significance was set at 0.05.

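### The trial is powered on the between-arm difference in FAC change, but the written between-arm test uses post-treatment values and leaves baseline FAC unused

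*Protocol article*

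**What the plan says.** The Sample size section is explicit about the endpoint: "The primary endpoint is the FAC difference before and after training". The planning effect is a contrast between arms in that change, since "the difference between the variation in the FAC of the test medical device and the comparator device was 0.71", and "the standard deviation was conservatively approached to assume the largest value of 1.4". The result is 65 per group for 80% power at two-sided 0.05.

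The Primary outcome section lists three visits and names no change score: "Primary endpoints are evaluated once in the baseline (pre-treatment), 4 weeks after the baseline (post-treatment), and 4 weeks after the last treatment (follow-up").

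The Statistical analysis section then gives three instructions for the outcomes:

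- Between arms, by t-test or Wilcoxon rank sum test: "the post-treatment measurement results will present the technological statistics, the observed number of patients, mean, SE, and range and compare the differences between groups".
- Within arms, by paired t-test or signed-rank test: "The comparison analysis of differences before and after treatment in the group will be conducted".
- ANCOVA, only if the check of baseline demographic and clinical characteristics suggests that some variable needs control.

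The Outcome measurements section describes the clinical characteristics as five screening criteria: diagnosis, cause, side of paralysis, MMSE criterion and MAS score. Baseline FAC is not one of them, although Table 1 shows that FAC is measured before treatment.

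**The concern.** Three quantities are in play: the post-treatment level compared between arms, the change tested inside each arm, and the change compared between arms. The trial is sized on the third. The analysis section describes only the first two.

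This matters for two reasons. First, the power statement belongs to a test that is not written down, so the power of the written test depends on a pre-post correlation that the article does not give. Second, the only tests written for the defined endpoint are within-arm tests, and these cannot show superiority. The planning figures themselves have the comparator arm improving by 0.54, so a before-after improvement is expected in both arms.

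The ANCOVA sentence does not close the gap. It depends on imbalance seen in the data, and the variables it draws on do not include baseline FAC.

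**Working it through.** **Inputs from the article (Sample size):** difference in change 1.25 − 0.54 = 0.71; SD 1.4; two-sided 0.05; power 80%; 65 per arm. **Assumed, because not given:** equal SDs of FAC before and after, and a pre-post correlation r of 0.4, 0.5 or 0.6.

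**Step 1. Reproduce the 65.** For a two-sample comparison of mean change:

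- Normal approximation: n = 2 × (1.960 + 0.842)² × 1.4² / 0.71² = 61.03, so 62 per arm.
- Exact t-test: 62.01, so 63 per arm.
- t-test figure divided by the rank-sum efficiency 0.955: 64.9, so 65 per arm.
- A one-sided test would give 49, which rules it out.

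The article does not name its formula, so the rank-sum allowance is an inference. Either way the stated size is that of a between-arm test of change. At 65 per arm the t-test on change has 81.8% power.

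**Step 2. SD that applies to each analysis.** Take the SD of change as s = 1.4. With equal SDs before and after:

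- Post-treatment values: SD_post = s / √(2(1 − r)).
- Change: s.
- ANCOVA on baseline: SD_post × √(1 − r²) = s × √((1 + r)/2).

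SD_post equals s exactly when r = 0.5. It is smaller below that and larger above. The ANCOVA SD is smaller than both of the others for any r between 0 and 1.

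**Step 3. Power at 65 per arm, difference 0.71, two-sided 0.05** (two-sample t-test; the one degree of freedom spent on the covariate is ignored):

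| r | SD post | SD ANCOVA | Power, post only | Power, change | Power, ANCOVA |
|---|---|---|---|---|---|
| 0.4 | 1.28 | 1.17 | 88% | 82% | 93% |
| 0.5 | 1.40 | 1.21 | 82% | 82% | 91% |
| 0.6 | 1.57 | 1.25 | 73% | 82% | 89% |

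Patients per arm for 80% power at the same three correlations are 52, 63 and 78 for post-treatment values, 63 for change throughout, and 44, 47 and 50 for ANCOVA.

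**Step 4. ANCOVA answers the powered question.** If post = a + b·arm + c·baseline, subtracting baseline from both sides gives change = a + b·arm + (c − 1)·baseline. The arm coefficient b is the same, so ANCOVA of the post-treatment value estimates the between-arm contrast in change.

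**The case against.** Much of the case on the other side stands.

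- **Validity.** Under 1:1 randomisation the expected between-arm difference in post-treatment FAC equals that in change. The written test is unbiased and keeps its 5% level. A reader might infer that chance baseline imbalance makes it invalid. It does not; it costs precision.
- **Type I error.** A reader might also infer an inflated false-positive rate from a choice between a post-value test and a change test. The article writes only one between-arm test per outcome at the post-treatment visit, so there is no second between-arm test to choose from.
- **Within-arm tests as efficacy evidence.** Nothing in the article says that the paired tests decide efficacy, and the Study design section states a superiority design. Labelling them descriptive is a safeguard.
- **Size of the loss.** Post-treatment values lose power against change only above r = 0.5. Higher correlations produce dramatic losses on paper, but with the change SD held at 1.4 they imply implausible FAC SDs: 1.81 at r = 0.7, wider than a uniform spread over six levels (1.71), and 2.21 at r = 0.8. At r = 0.9 the SD would be 3.13, above the maximum possible on a 1 to 6 scale, (6 − 1)/2 = 2.5. Those losses should not be used.
- **Wording and unseen text.** The between-arm sentence could loosely be read as comparing changes, and adjusted analyses are referred to a registry summary that is not shown. However, the sentence is about post-treatment measurements, and before-after differences have their own within-group sentence. The lists of baseline variables are introduced as examples, but the Outcome measurements section describes the clinical characteristics without FAC. Unseen text might add an adjusted analysis; it would not make these two sections agree.

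**Conclusion.** The Sample size and Statistical analysis sections do not name the same between-arm quantity. This follows from the text and needs no assumption. The written test is valid, but it is not the powered analysis and it leaves the measured baseline FAC unused.

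The size in power terms rests on equal SDs, a change SD of 1.4, 65 per arm and an assumed r of 0.4 to 0.6. Over that range baseline-adjusted ANCOVA gains about 5 to 17 percentage points over post-treatment values (93 − 88 = 5; 89 − 73 = 16 from rounded figures, 89.4 − 72.8 = 16.6 unrounded) and about 8 to 11 over change. Against the powered change test, the written test ranges from about 6 points better to 9 points worse.

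This should be fixed because the primary test of a superiority trial ought to be unambiguous and the better analysis is free. It does not invalidate the design.

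**What to change.** Name one primary between-arm analysis in the Statistical analysis section: ANCOVA of week-4 (post-treatment) FAC on arm, with baseline FAC as a covariate fixed in advance rather than chosen after an imbalance check. Report the adjusted mean difference with its 95% CI. Because FAC has six ordered levels, add an ordinal or rank-based equivalent as a sensitivity analysis. Label the paired within-arm tests descriptive.

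A plain between-arm test of change would also reconcile the two sections, but it would forgo the precision shown above.

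The cost is rewording. Baseline FAC is already collected, and no further patients or visits are needed. The Trial status section reports that recruitment is complete. If the data have already been analysed, the change should be disclosed and the result of the test as written shown alongside.

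### The primary FAC test is left to an unspecified normality check, which in practice yields a rank-sum test unadjusted for baseline FAC or centre, with no between-group estimate fixed

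*Protocol article*

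**What the plan says.** All references are to the protocol article.

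- **Primary outcome** describes the scale: "FAC is a variable that was evaluated by dividing by 1 to 6 depending on the degree of need for assistance when walking". It therefore has six ordered integer levels.
- **Sample size** defines the endpoint: "The primary endpoint is the FAC difference before and after training". It plans on means: "the difference between the variation in the FAC of the test medical device and the comparator device was 0.71", and "the standard deviation was conservatively approached to assume the largest value of 1.4". It adds "Two-sided tests were used for sample size estimation" but names no test. The number per group for "overall power of 80% under the significant level of 0.05 is 65".
- **Statistical analysis** handles the primary outcome with the continuous variables. Groups are compared by Student's t-test or the Wilcoxon rank-sum test, "depending on the satisfaction of the normality assumption". Number observed, mean, SE and range are reported whichever test is used. ANCOVA is added when the baseline homogeneity tests on demographic and clinical characteristics point to variables needing control. Baseline FAC and centre are not among the characteristics listed there.
- **Randomization and blinding** states that each institute has its own randomization file.

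**The concern.** The test that decides a superiority trial is to be picked after looking at the outcome data, by a check that is not defined. A second data-driven step, the imbalance-triggered ANCOVA, sits beside it, and the text does not say whether that result would replace or accompany the unadjusted one.

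Two things are at stake. The first is precision: the rule leads to a comparison that does not adjust for baseline FAC, which every patient has measured, or for centre, which structures the randomization. The second is interpretation: the trial is planned on a mean difference of 0.71 FAC levels, but a rank-sum p-value is not on that scale, and no between-group difference with an interval is named to go with it.

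**Working it through.** **Inputs from the Sample size section:** difference in mean change 1.25 − 0.54 = 0.71; SD 1.4; two-sided alpha 0.05; power 80%; 65 per group.

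**1. The stated 65.**
- Normal approximation: n = 2 × [1.4 × (1.960 + 0.842) / 0.71]² = 61.03, so 62.
- Exact noncentral t: 62.01, so 63.
- Rank-sum test, efficiency 3/π = 0.955 under a normal parent: 62.01 × π/3 = 64.9, so 65.

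The stated figure agrees with a rank-sum calculation. At 65 per group, exact t-test power is 81.8% and rank-sum power about 80%.

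**2. Will FAC pass a normality check?** The article gives no FAC distribution, so change is assumed to be a normal variable with mean 0.54, rounded to integers. Rejection at the 5% level:

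| Check | SD of change | n = 65 | n = 72 |
|---|---|---|---|
| Shapiro-Wilk, one arm | 1.4 | 98.8% | 99.6% |
| Shapiro-Wilk, one arm | 0.6 to 1.0 | 100% | 100% |
| Lilliefors (Kolmogorov-Smirnov corrected for estimated mean and SD) | 1.0 to 1.4 | 100% | 100% |
| Uncorrected Kolmogorov-Smirnov, one arm | 1.4 | 54% | 67% |
| Uncorrected Kolmogorov-Smirnov, either arm | 1.4 | 80–81% | 88% |

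Post-treatment FAC confined to levels 1 to 6 was rejected by Shapiro-Wilk in 100% of samples. Only the uncorrected Kolmogorov-Smirnov test, which is too conservative when mean and SD come from the same sample, passes with any frequency.

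**3. Cost of landing on the rank-sum test.** Simulated power on rounded change, SD 1.4:
- 65 per group: t-test 79.5%, rank sum 78.0%, a loss of 1.5 points.
- 72 per group: 85.3% and 83.0%, a loss of 2.3 points.
- A further simulation (realised difference 0.68, SD of change 1.35) gave 80.4% and 79.6%, a loss of 0.8 points.

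**4. Cost of no baseline adjustment.** With equal pre and post SDs and pre-post correlation r, the change score has variance 2σ²(1 − r) and the ANCOVA residual has σ²(1 − r²). The ratio is (1 + r)/2. Holding the SD of change at the planned 1.4, the ANCOVA SD is 1.4 × √[(1 + r)/2], and power at 65 per group is about Φ(0.71 / (SD × √(2/65)) − 1.96), with √(2/65) = 0.1754:

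| Analysis | SD | 0.71 / (SD × 0.1754) | Power |
|---|---|---|---|
| Change score, t-test | 1.400 | 2.89 | 82.4% |
| ANCOVA, r = 0.3 | 1.129 | 3.59 | 94.8% |
| ANCOVA, r = 0.5 | 1.212 | 3.34 | 91.6% |
| ANCOVA, r = 0.7 | 1.291 | 3.14 | 88.0% |

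Simulation on bounded, rounded FAC fixes the FAC SD instead, at an assumed 1.3, with 65 per arm and a realised difference of about 0.68. The SD of change before rounding is then 1.3 × √[2(1 − r)] = 1.54, 1.30 and 1.01, so all powers rise with r:

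| r | Rank sum on change | ANCOVA | Gain |
|---|---|---|---|
| 0.3 | 71% | 87% | 16 points |
| 0.5 | 83% | 91% | 8 points |
| 0.7 | 96% | 98% | 2 points |

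A separate run under the same assumed SD gave 73/83/95% and 87/92/97%. No figure is given for centre, because the article reports no between-centre variation.

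**The case against.** - **The two complaints pull against each other.** If the check practically always fails, the rule amounts to a fixed rank-sum test and there is little real choice. This stands. A reader might infer an inflated type I error, but nothing supports that: simulated under no effect with bounded FAC, the t-test rejected in 5.2% and the rank-sum test in 4.6% of trials. What remains is that the rule is undefined and leads to an inefficient comparison.
- **Failure is not literally certain.** This stands too. No normality test is named, and an uncorrected Kolmogorov-Smirnov test would sometimes pass. If that test is admissible, the primary method turns on chance, which is no defence of the rule.
- **The sample size.** A reader might infer that it rests on a t-test which will never be run. The article names no test, and 65 is the rank-sum figure. The match does not prove which method was used, but the switch does not undermine the number.
- **The estimate.** A reader might infer that no FAC difference will be available. Group means and SEs are reported in every case, so a crude difference can be derived, and the conditional ANCOVA would give an adjusted one. The point is only that none is fixed as primary with an interval.
- **The power gap belongs to baseline adjustment, not to the normality rule.** Correct: an unadjusted t-test on change would lose nearly as much. The correlation is also not in the article, hence the range above.
- **An article condenses.** It sends readers to the registry for adjusted analyses, which is not at hand. But the test-selection rule is stated in the article, so it can be judged as it stands.
- **ANCOVA on an ordinal score is partly a preference.** A prespecified rank-sum test would cure the data-dependence. It would not bring in baseline FAC or centre, or give a difference on the scale of 0.71.

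**Conclusion.** The point holds in a limited form. The primary test for a six-level ordinal outcome is left to an undefined normality check on the trial's own data. Under any valid common check the result will almost surely be a rank-sum test that adjusts for neither baseline FAC nor centre, and no between-group difference with a confidence interval is fixed beside it.

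The normality rule itself costs about 1 to 2.5 points of power, and the 65 per group stands. The larger avoidable loss is the missing baseline adjustment: 2 to 16 points in the simulations, depending on the correlation. Those figures rest on an assumed rounded, roughly normal FAC with SD 1.3 and correlations of 0.3 to 0.7; the article supplies none of these. The direction does not depend on the exact values, because (1 + r)/2 is below 1 for every correlation below 1 when pre and post SDs are equal.

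**What to change.** Before unblinding:

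1. Remove the normality check and the imbalance-triggered ANCOVA for FAC.
2. Name one primary analysis: ANCOVA of post-treatment FAC with baseline FAC and centre as covariates, reporting the mean difference and 95% CI with robust standard errors. With baseline FAC in the model, the treatment estimate is the same whether post-treatment FAC or its change is the response, so it still addresses the endpoint in the Sample size section.
3. Fix one sensitivity analysis that respects the ordinal scale: a proportional-odds model or a centre-stratified rank test (van Elteren).

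This needs no new data and no extra patients, since baseline FAC and centre are already recorded. The cost is a dated amendment to the analysis text. Timing matters: the Trial status section reports all 144 patients registered by 29 June 2020 and completion expected by the end of 2020. If outcomes have already been seen by arm, the new model can no longer count as prespecified and should be labelled accordingly.
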